### Sample size

This study employs three groups with a 1:1:1 ratio. The primary research indicator is HbA1c, where *α*=0.05, *β*=0.2, and considering a 20% dropout rate, the minimum sample size for a single group is 100 cases. Therefore, a total of at least 300 cases should be included in the three groups.

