### Statistical methods

All data will be entered separately by 2 members and analyzed after confirming complete agreement of data. SPSS 22.0 will be used for statistical analysis. All measures will be tested for normality using the Shapiro-Wilk method, and data that conform to a normal distribution will be statistically described using the mean ± standard deviation; data that do not conform to a normal distribution will be statistically described using the median (P25, P75), and correlation will be analyzed by Pearson correlation analysis, with differences considered statistically significant at P<0.05. Statistical descriptions of the different groups will be made using the mean, standard deviation, median, minimum, and maximum values for the different groups of measures. Statistical description of the count data of the different groups will be made using frequency (composition ratio). Changes before and after the intervention in each group will be calculated using exact probability or non-parametric tests. The analysis of dropout will statistically describe the actual number of subjects enrolled, the number of dropouts, and the number of dropouts one by one and analyze the specific reasons for dropout and dropout. Analysis of the balance of underlying values will use ANOVA or exact probability calculations to compare demographic information with other indicators of underlying values to measure the extent to which each group is in balance.

All patients who have received the behavioral economics-based digital intervention for at least 4 weeks will be included in the full analysis set (FAS). Depending on the timing of the survey, the analysis set following the study protocol (per-protocol, PP) will consist of patients who have completed a 3-month follow-up examination. The FAS will be used as the basis for the preliminary analysis. If the difference between the FAS and PP samples is greater than 10%, the analysis will be repeated for the PP analysis set. The safety population includes patients with FAS. Unless otherwise stated, all analyses will be performed on both the FAS and PP analysis sets. No additional analyses will be performed.

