Missing values will not be replaced or added. All analyses will be based solely on observed cases. Patients lost to follow-up will be considered to have dropped out of treatment. Only PP patients will be used in sensitivity analyses to test the impact of this assumption. No genetic or molecular analysis will be performed in this trial or future use.

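### The only sensitivity analysis for missing 3-month HbA1c uses 3-month completers, so it cannot show what informative dropout would do to the primary result

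*Protocol article*

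**What the plan says.** All of this is in the protocol article.

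- **Missing-data rule (Statistical methods):** "Missing values will not be replaced or added. All analyses will be based solely on observed cases". The next sentence treats patients lost to follow-up as having dropped out of treatment.
- **Check on that rule (same paragraph):** "Only PP patients will be used in sensitivity analyses to test the impact of this assumption".
- **PP set (Statistical methods):** it "will consist of patients who have completed a 3-month follow-up examination". The full analysis set (FAS) is defined separately, by at least 4 weeks of digital intervention, and is the basis of the main analysis. The section then excludes any further analyses.
- **Primary endpoint (Primary outcome measures):** HbA1c compared among the three groups at the 3-month follow-up.
- **Planned loss (Sample size):** "considering a 20% dropout rate, the minimum sample size for a single group is 100 cases", and "a total of at least 300 cases should be included in the three groups".

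**The concern.** A sensitivity analysis of a missing-data rule has to change what is assumed about the patients with no outcome. This one restricts the analysis to patients whose outcome was seen. For an endpoint measured at month 3, the observed-case rule has already made that restriction, so the second analysis largely repeats the first.

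The trial is open-label. Only groups A and B have app tasks, and their incentives depend on completion thresholds and SMBG diaries. It is plausible, though the protocol gives no data on it, that less engaged and less well controlled patients would leave A and B selectively. The remaining A and B patients would then look better than the groups as randomised. Two near-identical results would be reported as a robust finding, although the assumption that matters had not been tested.

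**Working it through.** **Step 1. Who is in each analysis of 3-month HbA1c**

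| Patient | FAS, observed cases | PP |
|---|---|---|
| At least 4 weeks of intervention, 3-month examination done | in | in |
| At least 4 weeks of intervention, no 3-month examination | out (no value) | out |
| Left before week 4, no 3-month examination | out | out |
| Stopped the program before week 4 but assessed at 3 months | out | in |

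Controls are assumed to enter the FAS by a matching rule, because the 4-week criterion refers only to the digital intervention. The two analyses can differ only through the last row. Those patients have observed outcomes, so they carry no information about the unobserved ones. Rows two and three, the patients at issue, are in neither analysis.

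**Step 2. Which assumption is being tested.** The wording could refer to the observed-case rule or to the sentence just before it, on patients lost to follow-up. A completers-only set contains no patients lost to follow-up, so it tests neither.

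**Step 3. How many patients.** The stated 100 per group fits 80 evaluable: 80 / (1 − 0.20) = 100. The full calculation cannot be reproduced, because the article gives no effect size or SD. The planned loss is 0.20 × 300 = 60 patients, leaving 240.

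**Step 4. Size of the undetected bias.** Let p be the fraction missing in an arm and g the mean HbA1c of its dropouts minus that of its completers. The completer mean differs from the full-arm mean by −p × g. The bias in a digital arm against C is therefore −(p_digital × g_digital − p_C × g_C). All values of g, and the unequal dropout rates, are assumptions.

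| p digital / p C | g digital / g C (points) | Bias (points) |
|---|---|---|
| 0.20 / 0.20 | equal | 0 |
| 0.20 / 0.20 | 0.5 / 0 | −0.20 × 0.5 = −0.10 |
| 0.20 / 0.20 | 1.0 / 0 | −0.20 × 1.0 = −0.20 |
| 0.30 / 0.10 | 0.5 / 0.5 | −(0.15 − 0.05) = −0.10 |
| 0.30 / 0.10 | 1.0 / 1.0 | −(0.30 − 0.10) = −0.20 |

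A negative sign favours the digital arm. If A and B are affected alike, the bias cancels in A against B.

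**Step 5. Scale.** The Sample size section gives "The primary research indicator is HbA1c, where *α*=0.05, *β*=0.2". I take α as two-sided, which is not stated. With 80 per arm and a two-sample t test, the detectable standardised difference is 0.446; the normal approximation (1.960 + 0.842) × √(2/80) gives 0.443. At an assumed SD of 1.0 to 1.5 this is 0.446 to 0.669, about 0.45 to 0.67 points. A bias of 0.10 to 0.20 is thus between 0.10/0.669 = 15% and 0.20/0.446 = 45% of the detectable difference.

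**Step 6. False-positive rate with no true effect.** With 80 observed per arm the standard error is SD × √(2/80), which is 0.158 at SD 1.0 and 0.237 at SD 1.5. The nominal 5% rate becomes:

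| Bias | SD 1.0 | SD 1.5 |
|---|---|---|
| 0.10 | 0.097 | 0.071 |
| 0.20 | 0.244 | 0.135 |

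A simulation of 5,000 two-arm trials (100 per arm, 20% missing in each, SD 1.0, g = 0.5 in the digital arm only, some dropouts leaving before week 4) gave a mean estimate of −0.10 and a rejection rate of 0.098. Everyone assessed at 3 months was in both sets, and the FAS observed-case and PP estimates were the same in every run, as Step 1 implies.

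**The case against.** The strongest reply is that the concern depends on dropout differing between arms, for which the protocol has no evidence. That is true of the size, and the zero-bias case belongs in the range. It does not rescue the check, which would give the same reassurance whether the bias was zero or 0.20.

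The protocol also limits missingness. Patients who stop the program remain eligible for assessment (criteria for discontinuing), investigators telephone about missing data (Data collection), and dropout numbers and reasons are reported. These steps may bring the loss below 20%, but none estimates the effect of the loss that remains.

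One might leave the matter to the analysis plan. Here, though, the article fixes the rule, names the sensitivity set and excludes further analyses, so a plan that supplied a proper check would contradict it.

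Three stronger readings are tempting and are not supported:

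- **FAS and PP are identical.** A reader might infer this, but they are defined differently and PP is not written as a subset of the FAS. Read literally, the FAS criterion would not admit controls at all, which is a separate matter. The overlap is specific to the observed 3-month outcome.
- **Observed-case analysis is biased here.** A reader might infer this too, but it is unbiased when dropout rates and dropout outcomes are alike across arms.
- **The PP rules plainly contradict each other.** One sentence says "If the difference between the FAS and PP samples is greater than 10%, the analysis will be repeated for the PP analysis set"; another says "Unless otherwise stated, all analyses will be performed on both the FAS and PP analysis sets". The opening words of the second allow the first to be an exception. Nor does 20% dropout mean that the 10% threshold will be crossed, since patients who leave before week 4 are outside both sets. This is unclear drafting and no more.

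**Conclusion.** The point holds in this form: the stated sensitivity analysis cannot do the job assigned to it. For 3-month HbA1c it re-analyses essentially the patients already in the main analysis and leaves out the roughly 60 of 300 whose outcomes are in question, on either reading of the assumption it is meant to test.

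The set logic rests on the protocol's own definitions plus one assumption, that controls enter the FAS by a matching rule. The size rests on assumed dropout shifts and an assumed SD: from no bias at all to about 0.10 to 0.20 points in the scenarios shown, against a detectable difference of about 0.45 to 0.67 points. These figures show what could pass unnoticed and do not predict that it will. Because the check bears on the credibility of the primary result and is inexpensive to replace, it should be changed before analysis.

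**What to change.** In Statistical methods:

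1. Replace the PP-only sensitivity analysis with one covering all randomised patients. Impute missing 3-month HbA1c by multiple imputation within arm, from baseline HbA1c, interim SMBG and weight data, and any interim HbA1c. The Primary outcome measures text has HbA1c at the end of every cycle, while Table 1 ticks it only at screening and the last visit, so the available interim values need to be confirmed.
2. Add a shift to the imputed values, set separately by arm over a range that includes zero. Repeat the primary comparison at each setting and report the shift at which the conclusion changes. This step does the testing. If HbA1c is measured only at baseline and month 3, imputation alone may add little.
3. Keep PP as a supplementary analysis, run unconditionally. That also settles the wording of the 10% trigger.
4. Amend the sentence that excludes further analyses so that it permits the above.

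The cost is a few extra analysis runs, a wording change and possibly slightly wider intervals. No additional data are needed.

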### Composition of the coordinating center and trial steering committee

Design and conduct of the study: preparation of the program and amendments; preparation of the Investigators’ Brochure (IB) and CRF; study to be published; composition of the TMC membership.

Steering Committee (SC): final protocol; recruit patients and communicate with the principal investigator; review the progress of the trial and agree adjustments to the protocol and/or investigator manual if necessary to help the study run smoothly. The steering group will include all principal investigators.

Trial Management Committee (TMC): (Principal Investigator, Study Physician, Administrator): study planning; conducts steering committee meetings; reports adverse events to the Chinese National Adverse Reaction Monitoring Centre; responsible for trial master file preparation; budget management and contract difficulties with individual centers; randomization; data validation; TMC will review 3 monthly feedback forms and arrange site visits; data manager: data entry and maintenance of clinical trial IT systems; data validation.

Lead Investigators: recruitment; data collection; CRF completion, study patient follow-up, and adherence to study protocol and IB.

### Composition of the data monitoring committee, its role, and reporting structure

There will be no data monitoring committee for this study because the intervention in this study is considered a low-risk intervention.

### Interim analyses

There will be no interim analysis.

### Adverse event reporting and harms

Any adverse events that occurred between the time the subject signed the informed consent and was enrolled in the study and the end of the study, regardless of whether there was a causal relationship with the intervention. Any medical condition or clinically significant laboratory abnormality occurring prior to the administration of the intervention on day one is considered pre-existing and must be documented on the case report form. All AEs occurring after the administration of the intervention up to the last day of the study (including follow-up, the pause period of the study) must be recorded as AE subsets in the appropriate CRF section. When completing the adverse event form in the CRF, the investigator will use a scale of “1 to 5” to describe the severity of the adverse event. To standardize the criteria, the intensity of the adverse event will be judged by reference to the CTCAE v3.0 grading definitions: Grade 1 (mild, asymptomatic, or with mild signs; clinical or diagnostic observations only; no intervention required), Grade 2 (moderate, requiring minimal, local or non-invasive treatment, age-appropriate instrumental limitation of activities of daily living), Grade 3 (severe or clinically significant but not immediately life-threatening; hospitalization or prolonged hospitalization; disabling; limited ability to perform activities of daily living), Grade 4 (life-threatening, requiring urgent treatment), Grade 5 (death). The type and frequency of any adverse event will be reported to the Chinese National Adverse Reaction Monitoring Centre.

### Frequency and plans for auditing trial conduct

The audit process will comply with ICH GCP and regulatory requirements. Twice yearly audits will be conducted by the Hospital Ethics Committee and the audit process will be independent of the Sponsor. The SC will decide on any revisions to the program. The revised protocol will also be submitted to the Medical Ethics Committee of Kunshan First People’s Hospital and reported to the participants as and when required. The results of this study will be presented to the public at an academic conference. Authorship will be determined by the Steering Group. The order of authorship will be determined by the contribution of each member.

## Discussion

This paper describes in detail a parallel randomized controlled trial designed to assess the impact of digital intervention based on behavioral economics theory on indicators such as HbA1c, SMBG detection rates, and diabetes self-efficacy in patients with T2DM. Digital health care has been widely used in health systems, particularly during the COVID-19 pandemic, and to reduce the risk of virus transmission between patients and clinicians, many health systems have rapidly converted more than 70% of outpatient cases to digital care via telephone or video transmission [20, 21]. However, concerns remain that chronic disease management delivered through digital processes may be of poor quality, difficult for patients to use proactively and spontaneously, and may exacerbate health disparities. To improve digital chronic disease management even more, we think that digital intervention based on behavioral economics theory is a feasible way to improve HbA1c levels in patients with T2DM. Such digital interventions integrate multidisciplinary theories. We hypothesized that digital intervention based on behavioral economics theory would be effective in improving SMBG detection rates and diabetes self-efficacy in T2DM patients. The significance of this study is that, until now, research on digital intervention and patients with T2DM has been limited to the hospital setting. No studies have yet reported the effectiveness of digital intervention based on behavioral economics theory in T2DM patients outside the hospital. As behavioral economics theory highlights that people are influenced by cognitive biases and emotional factors when making decisions, the intervention process will be gamified and is expected to increase patients’ interest in using it. In addition, this study may demonstrate that a digital intervention based on behavioral economics theory can reduce the financial burden on T2DM patients. Moreover, there are some limitations to this study. This study excluded T2DM patients treated with multi-drug combinations and only included T2DM patients who were stably treated with mono-therapy. Future studies may involve a larger group of patients. Secondly, due to the nature of the study, it was not possible to use blinding among participants and staff (excluding statisticians) during digital administration, which may have biased the expected effect of treatment.

### Trial status

The present protocol is version 1.0, dated September 26, 2022. Participant recruitment has began on April 15, 2023, and is expected to be completed by December 15, 2023.

## Data Availability

Not applicable.

## Abbreviations

T2DM: Type 2 diabetes mellitus
HbA1c: Glycosylated hemoglobin
SMBG: Self-monitoring of blood glucose
EDC: Electronic data capture
IDF: International Diabetes Federation
ICT: Information and communication technology
CBT: Cognitive behavior therapy
MeSH: Medical subject headings
SPIRIT: Standard Protocol Items: Recommendations for Interventional Trials
WHO: World Health Organization
TMC: Trial Management Committee
CRF: Case Report Form
CRC: Clinical research coordinator
DM: Data Manager
ICH GCP: International Conference on Harmonisation Good Clinical Practice Guidelines
FAS: Full analysis set
PP: Per-protocol
IB: Investigators’ Brochure
SC: Steering Committee
TMC: Trial Management Committee
AE: Adverse event
CTCAE: Common Terminology Criteria for Adverse Events
COVID-19: Coronavirus disease 2019
